### Recruitment {15}

Eligible participants from the DAPP cohort will be approached during a visit at the outpatient clinics at the participating pediatric departments. Alternatively, potential participants from the DAPP cohort that have been identified after review of their medical notes can be contacted by letter containing a brief description of the trial and asked if they could be interested in more information about and potentially participation in the LIFE-MET trial. Informed consent from all parental authority holder(s) and assent from the children will be obtained prior to undertaking any trial-related procedures.

## Methods: assignment of interventions

### Allocation

#### Sequence generation {16a}

A block randomization list will be created for each center by our data manager (using Sealed Envelope™, www.sealedenvelope.com), at no point available for personnel enrolling participants. Blocks will consist of either 4 or 8 participants. Participants will be randomized using stratified permuted block randomization. First, participants will be divided into strata (center), and then block randomization in the four trial arms (Fig. 1) will be performed for each stratum.

#### Concealment mechanism {16b}

Random allocation to a group will be performed in REDCap upon the baseline visit, using the computer-generated allocation sequence. When clicking “randomization” in REDCap, a code and “Lifestyle intervention: YES/NO” will appear. In the locked medicine room, the investigator can find an envelope with the designated code containing tablets of either metformin or placebo.

#### Implementation {16c}

Participants and their parents will be informed, enrolled in the trial, and randomized by the recruiting investigator who will remain blinded to the allocation of metformin or placebo during the entire study period.

### Blinding

#### Who will be blinded after assignment to interventions {17a}

The pharmacy will receive the allocation list from our data manager and will label and pack the placebo and the metformin accordingly. The placebo and the metformin will be identical in appearance and will be sourced in identical packages with similar labels.

The patient, investigator, and all study and project management staff will be blinded to treatment allocation with metformin or placebo. Allocation to lifestyle intervention cannot be blinded and will thus appear as “Lifestyle intervention: YES/NO” upon allocation.

#### Circumstances under which unblinding is permissible {17b}

If an adverse event should lead to termination of the trial, or if a participant/parent wishes to withdraw from the intervention, the participant will be invited to continue to attend trial visits and to complete all trial assessments. After completion of the trial, the treatment allocation can be revealed.

In case of the need for emergency unblinding, either the data manager or a designated colleague not related to the trial can be contacted via the coordinating investigator. Only these two persons will have access to the allocation list.

## Methods: data collection, management and analysis

### Data collection and assessment of outcomes {18a}

See Fig. 2.

The primary outcome of this trial is defined as the difference in bone age (days) over 1 year determined by automatic bone age determination (BoneXpert, Visiana, Denmark [54]). An X-ray of the left hand and wrist will be performed at baseline, 6 months, and 12 months. At each center, the same version of the BoneXpert program will be employed for the determination of bone age (version 3; 2021). This method defines bone ages by Greulich & Pyle and Tanner-Whitehouse.

Secondary and exploratory outcomes:Clinical variables will be collected by an experienced pediatric team (pediatric endocrinologist and nurse) at baseline and at 3, 6, and 12 months: pubertal staging (Tanner stage), anthropometry (height, weight, BMI, waist-hip circumference, and ratio), systolic blood pressure (BP), and heart rate (HR).Body composition will be assessed by a DXA at baseline and again at 6 months and will include body fat percentage, lean mass, and gynoid/android fat distribution (g/%).Fasting blood samples (sex hormones, metabolic markers, and safety parameters) will be collected at baseline and again at 3 and 6 months. The maximum amount of blood drawn at each visit will be 40 ml. Safety parameters (Na, K, urea, creatinine and ALAT, bilirubin) will be analyzed immediately at the local clinical laboratories. The analyses for research purpose will be performed centrally after collection of all samples during the 2 years of inclusion. At first, the samples will be centrifuged, labeled, frozen, and stored in a research biobank at each hospital coordinated by Bio- and Genome Bank, Denmark (RBGB). The biological material will be frozen at either −20 °C or −80 °C in a locked freezer. After end of the trial and sample collection, all the serum samples in the research biobanks will be transferred to and stored in the permanent freezer facility in the Capital region (BIOSEK) so they are available for the planned analyses in the project.Age at menarche: Questionnaire on occurrence of menarche from the 12 month-visit and until menarche, sent biannually.Fitness and activity outcomes:oFitness level (aerobic performance and explosive strength) will be evaluated for all participants prior to and after cessation of the intervention period using the following validated tests adapted to children: standing long jump (centimeters), a 20-m sprint (seconds), and the YYIR1C (Yo-Yo Intermittent Recovery Level 1 for Children, meters) [53].oDaily physical activity level will be tracked (SENS Motion® activity tracker) for 1 week prior to and after cessation of the intervention period. Activity level will be given as percentage time spent in different activity categories (i.e., rest, moderate intensity) on average.oDaily steps taken: Participants in the lifestyle intervention groups will be asked to wear a fitness watch every day during the 6 months intervention period and to record the number in a diary.Quality of life: Participants and their parents will be asked to fill out the WHO-5 Well Being Questionnaire on quality of life before and after the intervention.

### Plans to promote participant retention and complete follow-up {18b}

During the intervention period, participants will be seen with 3-month intervals. In addition, a telephone interview will be performed after 1 month of recruitment. This close contact with participants should facilitate adherence to the intervention and reduce the risk of lost to follow-up.

### Data management {19}

Data will consist of numerical data (clinical data including blood samples, calculated bone age, values from DXA, results from fitness tests, and activity level), imaging data (X-rays, DXA), and information from questionnaires. All research data will be entered in pseudo-anonymized form (patient ID generated in REDCap) and will be stored in a REDCap database. The trial database will be protected by a security code, and only registered users with a password will have access.

Blood sample results (safety parameters), X-rays, and some clinical data (e.g., anthropometry) will in addition be stored in the electronic patient journal. Electronic questionnaires will be sent directly to REDCap.

We will perform repeated monitoring of data to identify eventual missing data and to ensure the accuracy of data in order to intervene if necessary.

### Statistical methods {20a}

The statistical analyses will be performed using the program R (R version 4.3.2, 2023 or later, The R Foundation for Statistical Computing). We will apply linear mixed-effects models to assess the effect of the intervention (± metformin, ± lifestyle) on the primary endpoint: changes in bone age (days). Furthermore, we will employ mixed-effects models to assess the effect of the intervention on the secondary outcome measures: breast development, sex hormones, insulin sensitivity, metabolic markers, fitness level, and body composition within and between treatment groups as well as age at menarche. Model assumptions for both linear and logistic mixed regression models will be assessed, including, where appropriate, checks for linearity, multicollinearity, random effects normality, and residual diagnostics.

Statistical analysis will be done separately for participants who complete follow-up (per-protocol) and the intention-to-treat population. Only participants that complete the intervention (have taken a minimum of 80% of the pills and participated in a minimum of 80% of the eventual allocated lifestyle intervention) will be part of the per-protocol population. Participants must in addition complete a minimum of the baseline visit and the follow-up visit at 12 months. A *P* value of <0.05 will be considered statistically significant. Estimates of treatment effects will be presented with 95% confidence intervals.

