**Methods:**

LIFE-MET is a randomized, placebo-controlled, four-arm, multicenter trial of girls (*n* = 80) with overweight and early puberty. Allocation to metformin or placebo will be double-blinded. Eligible girls will be randomly assigned to one of the four study arms: Metformin + lifestyle intervention (*N* = 20), Metformin alone (*N* = 20), Placebo + lifestyle intervention (*N* = 20), Placebo alone (*N* = 20). The intervention period is 6 months with a follow-up after an additional 6 months. The primary outcome is the change in bone age from baseline to 12 months, as a marker of pubertal progression. Secondary outcomes include changes in body composition, Tanner stage, fitness level, sex hormones, insulin resistance, and age at menarche.

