### Trial design {8}

The participants will be recruited from the DAnish Precocious Puberty study (DAPP study, Clinical Trial number NCT05957991) which is a nationwide longitudinal cohort study including children with early puberty to determine the incidence of central precocious puberty and to explore the impact of lifestyle and environmental factors on the timing of puberty. The DAPP study, which was initiated on December 1, 2023, will include all children referred for precocious puberty to each of the 17 pediatric departments in Denmark during a 3-year period.

LIFE-MET is a randomized, placebo-controlled, four-arm, multicenter trial with a 1:1 allocation ratio of a sub-cohort (*n* = 80) of participants from the DAPP study. The trial is a superiority trial comparing metformin to placebo. Allocation to metformin or placebo will be double-blinded. Eligible girls will be randomly assigned to one of the four trial arms: Metformin + lifestyle intervention (*N* = 20), Metformin alone (*N* = 20), Placebo + lifestyle intervention (*N* = 20), Placebo alone (*N* = 20). The intervention period is 6 months with follow-up after an additional 6 months.

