### Sample size {14}

Sample size was calculated using a study of girls with low birth weight who had early puberty and were treated with metformin. This treatment delayed pubertal progression, and age at menarche was 11.4 (SD 0.69) years in untreated girls and 12.5 (SD 0.44) years in metformin-treated girls (*P* < 0.0001) [38]. This difference is equal to 1 SD of age at menarche in Danish data. The former study used a lower dose of metformin, but the participants were treated for a longer period. Using a more conservative approach with a change of 0.5 SD in age at menarche (equivalent to delaying menarche from 11.4 (SD 0.69) years to 11.9 years), we found that with a significance level of 5% and power of 90%, there should be 80 girls (40 in each treatment group (metformin/placebo)) included to detect a difference. However, our primary outcome is change in bone maturation (change in bone age) as an earlier surrogate measurement of age at menarche because it describes pubertal progression. No other studies have explored the effect of metformin on pubertal progression determined by changes in bone age which hinders a sample size calculation based on the primary outcome. We therefore plan to include 80 girls (metformin (*n* = 40) or placebo (*n* = 40)). We will use an intention-to-treat approach, and data from all randomized subjects will be included in the statistical analysis.

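### Within-group change is named as a way to assess the intervention's effect on secondary outcomes, though girls in puberty change without treatment; the classes of two outcomes also disagree

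*Protocol article*

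**What the plan says.** The analysis of secondary outcomes stands in Statistical methods {20a}: "we will employ mixed-effects models to assess the effect of the intervention on the secondary outcome measures". The list that follows includes "sex hormones, insulin sensitivity, metabolic markers, fitness level, and body composition within and between treatment groups". Within-group change is thus one of two named ways of assessing the intervention, and nothing marks it as descriptive. The next paragraph gives one general decision rule, a P "value of <0.05 will be considered statistically significant", and promises 95% confidence intervals for treatment effects. The sentence on the primary endpoint refers to metformin and lifestyle, present or absent, and does not say 'within'.

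The design is comparative. Trial design {8} states: "Eligible girls will be randomly assigned to one of the four trial arms", with 20 girls per arm, and calls the trial a superiority trial of metformin against placebo.

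The classes of two outcomes differ between sections:

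- Abstract, Methods: "Secondary outcomes include changes in body composition, Tanner stage, fitness level, sex hormones, insulin resistance, and age at menarche". Fitness level is secondary here; metabolic markers are not mentioned.
- Outcomes {12}: fitness level and metabolic markers are both exploratory.
- Statistical methods {20a}: both are among the secondary outcome measures.
- Objectives {7}: both are named in the secondary objectives.

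**The concern.** A within-arm test asks whether an outcome moved from baseline. It cannot say why. Inclusion requires breast development at Tanner B2 or above and LH above a threshold, so breast stage and sex hormones are expected to change in every arm. The background describes normal puberty as a time of insulin resistance, so HOMA-IR may shift too, and body composition may do the same. In the placebo-alone arm there is no active intervention whose effect such a test could assess.

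As written, a significant change within a metformin or lifestyle arm could be reported as an effect of the intervention on a secondary outcome, without a randomised comparison behind it. The differing classes add a smaller problem: fitness level and metabolic markers could be reported as secondary or exploratory, with support in the protocol for either.

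**Working it through.** **1. The plan's own figure.** Sample size {14} states: "with a significance level of 5% and power of 90%, there should be 80 girls", that is, "40 in each treatment group (metformin/placebo"). The assumed effect is "equivalent to delaying menarche from 11.4 (SD 0.69) years to 11.9 years", a difference of 0.5 years.

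n per group = 2 × [SD × (z₀.₉₇₅ + z₀.₉₀) / difference]² = 2 × [0.69 × (1.960 + 1.282) / 0.5]² = 40.02.

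The stated 40 per group is reproduced to rounding (strictly rounded up, 41), and power at 40 per group is 0.900 by the normal formula. This calculation is for a between-group comparison.

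**2. Within-arm test with no treatment effect.** Inputs:

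- 20 girls per arm (Trial design {8}) and 40 per metformin or placebo group (Sample size {14}).
- Significance level 5% (Statistical methods {20a}), taken as two-sided because the sidedness is not stated.
- Natural change d, in SDs of the change score, equal in all arms. The protocol gives no value; 0.2 to 1.0 is assumed.

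The test is a one-sample t-test on change from baseline, with n − 1 degrees of freedom and noncentrality d√n. It is a simple stand-in for the within-arm contrast of a mixed model with complete data.

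| d (SD) | d√n, n = 20 | P(significant), n = 20 | d√n, n = 40 | P(significant), n = 40 |
|---|---|---|---|---|
| 0 | 0 | 5% | 0 | 5% |
| 0.2 | 0.89 | 13.6% | 1.26 | 23.5% |
| 0.3 | 1.34 | 24.7% | 1.90 | 45.7% |
| 0.5 | 2.24 | 56.5% | 3.16 | 86.9% |
| 0.8 | 3.58 | 92.4% | 5.06 | 99.9% |
| 1.0 | 4.47 | 98.9% | 6.32 | 100% |

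**3. Between-group test on the same changes.** Two groups of 40, no treatment effect, 50,000 simulated trials per setting: significant in 4.97% (d = 0.3), 5.03% (d = 0.5) and 4.89% (d = 1.0). The common change cancels, so the error rate stays at about 5% whatever d is.

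**4. Outcome classes.** No arithmetic applies. Outcomes {12} conflicts with the abstract and Statistical methods {20a} on fitness level, and with Statistical methods {20a} on metabolic markers. Objectives {7} fits the secondary label for both.

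**The case against.** The strongest reply is that the sentence loosely describes what a mixed model yields, namely change over time in each group and contrasts between groups. The between-group comparison is in the same sentence, confidence intervals for treatment effects are promised, and the trial is declared a superiority trial. All of this is true, and it limits the point: the randomised comparison is not missing and the primary endpoint is untouched. It does not remove the fault, because the sentence gives the whole phrase the task of assessing the intervention's effect.

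A reader might infer that the trial will claim efficacy where one arm is significant and another is not. The protocol states no such rule, and the P value sentence is general. How often arms would disagree also depends on the unknown natural change. With two groups of 40 and no treatment effect, the chance 2p(1 − p) is 50% at d = 0.3 but 23% at d = 0.5 and near zero at d = 0.8. No weight is put on it here.

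A reader might also extend the point to the number of secondary outcomes tested. That question arises equally for valid between-group tests and is commonly left to the statistical analysis plan, which is not shown.

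Two further limits stand. Natural change is well founded for breast stage and sex hormones, less certain for insulin sensitivity and body composition, and a mere assumption for fitness and metabolic markers. The period is also short for most outcomes: Data collection {18a} takes blood and DXA up to 6 months and fitness before and after the 6-month intervention. Breast staging runs to 12 months but is expressed as a puberty Z-score, whose natural change may differ from that of the stage itself.

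**Conclusion.** The point holds for secondary outcomes only. Statistical methods {20a} gives within-group change a role in assessing the intervention that it cannot fill in girls already in puberty. With no treatment effect, a within-arm test would be significant in about 14% to 99% of cases at 20 per arm and 24% to 100% at 40 per group, against about 5% for the randomised contrast. These ranges rest on an assumed natural change of 0.2 to 1.0 SD, equal in all arms, and on two-sided 5% tests. The documents do not support the stronger reading that the randomised comparison is absent or that the primary analysis is affected. The mismatch in the class of fitness level and metabolic markers is a separate contradiction that needs no assumption. Both should be corrected before analysis.

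**What to change.** In Statistical methods {20a}, delete 'within and'. State that all treatment-effect statements for secondary outcomes rest on the randomised contrasts (metformin against placebo, lifestyle against none) with the 95% confidence intervals already promised. Report within-arm changes as descriptive summaries without P values.

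Separately, choose one class for fitness level and use it in the abstract, Outcomes {12} and Statistical methods {20a}. Choose one class for metabolic markers and use it in Outcomes {12} and Statistical methods {20a}; the abstract does not list them and needs no change on that account. Then check both against the secondary objectives in Objectives {7}.

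The cost is wording only: no new data, visits or girls. Recruitment is expected to end in February 2027 and no interim analysis is planned, so the change can be made and dated before any analysis.

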##### Medication intervention

Metformin subgroups: Trial dose will be 1000 mg daily (1 scored tablet). Initiation dose will be 500 mg (½ tablet) for the first 14 days to avoid or mitigate adverse effects. The treatment period will last for 6 months in total (180 days).

Placebo subgroups: The placebo dose will be ½ tablet once daily for 14 days, and then 1 tablet once daily for the remaining period. The treatment period will last for 6 months in total (180 days).

The tablets containing the active substance (metformin) and those containing placebo will be indistinguishable from one another with the same shape, size, and color and will both have a score line.

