#### Strategies to improve adherence to interventions protocols {11c}

Participants will be contacted by telephone after 1 month and will be seen every 3 months during the treatment period to maintain close contact and to monitor adherence and adverse events. In addition, participating girls and their families will be asked to fill out a short daily diary including adherence (tablets taken). Ultimately, adherence will be registered when participants return any unused medication after the intervention has ended (ratio between tablets dispensed and tablets returned by the patient at 6 months).

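### One per-protocol set serves both contrasts, but its attendance filter can remove only lifestyle-arm girls, and the stated tablet ratio does not match the 80% pill rule

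*Protocol article*

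**What the plan says.** Statistical methods {20a} assesses the effects of metformin and of lifestyle with mixed models and introduces two analysis sets: "Statistical analysis will be done separately for participants who complete follow-up (per-protocol) and the intention-to-treat population". It then says who belongs to the per-protocol set. A girl must "have taken a minimum of 80% of the pills" and must have "participated in a minimum of 80% of the eventual allocated lifestyle intervention". The section adds: "Participants must in addition complete a minimum of the baseline visit and the follow-up visit at 12 months". No separate set is given for the metformin and lifestyle questions, and the section does not say which of the two analyses is supportive.

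Adherence is described in Strategies to improve adherence {11c}. Families keep a daily diary of tablets taken, and unused medication is handed back at the end, with adherence registered as the "ratio between tablets dispensed and tablets returned by the patient at 6 months". {20a} does not say which of these sources feeds the 80% pill rule.

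Trial design {8} describes a superiority comparison of metformin with placebo, and Objectives {7} makes that the primary objective; the lifestyle effect is secondary. Sample size {14} and the analysis population section {20c} commit to intention-to-treat on all randomized girls.

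**The concern.** The pill and visit conditions apply to all four arms. The attendance condition applies only where there is something to attend, in arms 1a and 2a. Using the same set for both contrasts has two consequences.

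- **Lifestyle versus no lifestyle.** One side is selected after randomization on sustained attendance at training and the other is not. Girls who keep up a twice-weekly programme for six months may differ from those who do not in ways that also affect pubertal progression. A difference could then appear without any lifestyle effect.
- **Metformin versus placebo.** Girls who took their tablets as prescribed are dropped for missing exercise sessions, which says nothing about adherence to the drug. The set becomes smaller than the question requires and its mix shifts towards girls without the lifestyle programme.

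The tablet ratio in {11c} adds a smaller problem: the quantity it describes is not the percentage that {20a} needs.

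**Working it through.** **Plan's own figure.** Sample size {14} gives a difference of 0.5 years, SD 0.69, 5% significance, 90% power and 80 girls. Two-sided, n per group = 2 × [0.69 × (1.960 + 1.282) / 0.5]² = 40.02. Rounded up this is 41 per group (82 in total), and power at 40 per group is 90.0%. The plan's 80 is reproduced.

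**Metformin contrast.** Each medication group has 20 lifestyle and 20 non-lifestyle girls ({11a}). Let p be the share meeting the pill rule and a the share of pill-adherent lifestyle girls meeting attendance. The documents give neither, so both are assumed. Everyone is taken to attend the 12-month visit.

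- As written: m = 20p + 20pa per medication group. Without the attendance filter: m = 40p.
- Power = Φ(0.5 / [0.69 × √(2/m)] − 1.960).
- Example, p = 0.8, no filter: m = 32, SE = 0.69 × √(2/32) = 0.1725, power = Φ(2.899 − 1.960) = 82.6%.

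| Attendance a | m at p = 80% | Power | m at p = 100% | Power |
|---|---|---|---|---|
| no filter | 32 | 82.6% | 40 | 90.0% |
| 80% | 28.8 | 78.5% | 36 | 86.7% |
| 60% | 25.6 | 73.6% | 32 | 82.6% |
| 50% | 24 | 70.9% | 30 | 80.1% |
| 40% | 22.4 | 67.9% | 28 | 77.4% |

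These powers use the age-at-menarche effect because the protocol gives none for bone age, the primary outcome.

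**Lifestyle contrast.** At p = 80% and a = 50%, the set holds 40 × 0.8 × 0.5 = 16 lifestyle girls against 40 × 0.8 = 32 others. Lifestyle girls fall from half of the set to 16/48 = 33%.

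To illustrate the selection, suppose that the tendency to attend is normal and correlates r with outcome. The mean shift among the attending share a is r × φ(c)/a, where c is the cut-off exceeded by a share a. At a = 50% this is 0.798r, or 0.08, 0.16 and 0.24 SD for r = 0.1, 0.2 and 0.3. Both r and a are assumed. The formula treats the comparison girls as unselected on that tendency; if pill-taking and visit completion go with it, the gap is smaller.

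**Tablet ratio.** The schedule in {11a} is "½ tablet once daily for 14 days, and then 1 tablet once daily for the remaining period", over 180 days. That makes 14 × ½ + 166 × 1 = 173 tablets. If exactly 173 are dispensed:

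- Full adherence: dispensed/returned = 173/0, undefined.
- 80% adherence: returned = 34.6, so dispensed/returned = 173/34.6 = 5.0, and the inverse is 0.20.
- (dispensed − returned)/prescribed = 138.4/173 = 0.80, which is the figure the rule needs.

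The denominator also matters. The quantity dispensed is not stated. If it were 200, a girl who took 138.4 tablets would return 61.6. Then (200 − 61.6)/200 = 69%, against 80% of tablets prescribed.

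**The case against.** - **Controls are filtered too.** This stands: the pill and visit rules apply to every arm. A reader might infer that motivated lifestyle girls are compared with wholly unselected controls, and the text does not support that. The asymmetry is confined to attendance.
- **The primary contrast is not biased.** This stands. Lifestyle is allocated 20 and 20 within each medication group, and the same rule falls on both. Bias would require attendance to depend on the drug, which nothing in the protocol shows. The shift in mix matters only if the metformin effect differs by lifestyle.
- **The set can be built.** This stands. A reader might conclude that the 80% rule cannot be applied at all. But the wording fixes no order for the ratio; if dispensed equals prescribed, the share taken is 1 − 1/(dispensed/returned); and the diary is a second source. The fault lies in the formula and the unnamed source, since the data are collected.
- **There is one per-protocol population.** The opening phrase about completing follow-up could be read as a second, wider set. The following sentences read more naturally as its definition, so this is a loose label.
- **Intention-to-treat governs, and requiring adherence to whatever was allocated is conventional.** The first part stands. Convention does not resolve the second: in a factorial layout, adherence to the whole package is not adherence to the factor being tested.
- **Details may sit in an analysis plan that is not shown.** This is fair for the source order and the supportive label. It does not cover the attendance condition or the ratio, which this protocol states itself.

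**Conclusion.** The point holds, and is limited to the per-protocol analysis. The per-protocol lifestyle contrast is selected on one side after randomization and cannot be read as a randomized comparison; the size of any resulting bias is unknown. For metformin versus placebo the established cost is precision and a shift in the lifestyle mix. At 80% pill adherence and 40–80% attendance, 22.4–28.8 girls per medication group remain instead of 32, with power of about 68–79% instead of 83%. At the favourable end the loss is only about 4 percentage points. These figures rest on assumed adherence and on a planning effect for age at menarche. The tablet ratio as worded is not the share of pills taken and needs correcting. The intention-to-treat results are unaffected. The documents do not support reading this as a biased primary result or as a set that cannot be constructed.

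**What to change.** 1. For metformin versus placebo, define per-protocol by the pill rule and the baseline and 12-month visits in all four arms, with lifestyle as a factor and no attendance condition.
2. Base the lifestyle conclusion on intention-to-treat. Label any attendance-filtered lifestyle result as exploratory and open to selection.
3. In {11c}, state adherence as (dispensed − returned) / tablets prescribed for that girl, and say whether the count or the diary decides when they disagree. A fixed denominator of 173 should not be written in, because {11b} provides for instructed pauses in treatment.
4. In {20a}, align the opening description of the per-protocol set with the definition that follows, and state that per-protocol is supportive to intention-to-treat.

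These are wording changes that use data already collected, best made before unblinding. The one downside is that the metformin per-protocol set would no longer represent adherence to the full allocated package.
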